## Abstract

**Background:**

Fatigue has a profound negative impact on health for adults with end-stage kidney disease (ESKD) who receive maintenance hemodialysis. There are currently no standard-of-care therapies to alleviate this fatigue. Progressive muscle relaxation and physical activity have decreased fatigue in other populations. In collaboration with a patient partnership board, we developed an intervention aimed at reducing fatigue for adults receiving maintenance hemodialysis (*Fight Fatigue*), and we describe the protocol for its feasibility trial.

**Methods:**

*Fight Fatigue* was informed by our formative work with a patient partnership board (n = 3). Three virtual meetings were held, followed by 1:1 interviews with each board member. During the meetings, qualitative data was collected about the board's experience with fatigue and their feedback on the components of the intervention, which focused specifically on progressive muscle relaxation and increasing steps per day, as well as the study procedures. The *Fight Fatigue* intervention was developed informed by these findings. In the planned feasibility trial of this intervention, participants will be enrolled and randomized to either the *Fight Fatigue* intervention or an attention control. Data will be collected at baseline, week 6, and week 12. For this trial, the primary study endpoints are feasibility and acceptability, with a secondary endpoint of fatigue.

**Conclusion:**

The findings of this feasibility trial will inform the development of a randomized controlled trial of a combined mind-body and physical activity intervention to address fatigue for adults with ESKD receiving hemodialysis.

**Clinicaltrials gov:**

NCT07014111.

## Introduction

1

Fatigue affects up to 97% of adults with end-stage kidney disease (ESKD) receiving hemodialysis and is reported to be one of the most concerning symptoms [1,2]. Fatigue has a negative impact on morbidity, quality of life, social relationships, and functional independence in those with ESKD [[3], [4], [5], [6], [7], [8], [9], [10], [11]]. There are no standard-of-care therapies to alleviate the fatigue experienced by those with ESKD [3,4,12]. Progressive muscle relaxation, which involves the mindful tensing and releasing of muscles, has been found to relieve fatigue in chronic disease populations but has been minimally studied in those with ESKD [[13], [14], [15], [16], [17], [18], [19], [20], [21]]. There is also robust evidence that walking can significantly reduce fatigue for adults with chronic illnesses [[22], [23], [24]].

To develop an intervention to meet the needs of those with ESKD, it is necessary to integrate the patient perspective, which can be facilitated through a patient partnership board [[25], [26], [27]]. Patient partnership boards have helped develop interventions for adults with ESKD [[27], [28], [29]]. This study seeks to extend this work by co-developing, with a patient partnership board, a combined progressive muscle relaxation and walking intervention to reduce fatigue in adults with ESKD receiving maintenance hemodialysis. Here we describe this formative work, as well as outline the design and methods of the feasibility trial of the fatigue-reducing intervention.

## Formative work

2

For our formative work, we worked with a patient partnership board to inform patient-centered adaptation of a fatigue-reducing intervention and to enhance intervention feasibility and relevance for adults with ESKD. The role of the board was to act in a consultative capacity providing feedback, insight, and suggestions on how to adapt the intervention to meet the needs of those with ESKD. Three individuals with ESKD receiving maintenance hemodialysis were recruited via purposive sampling and enrolled as members of a patient partnership board in 2025. The board was kept to three individuals because the board members preferred to participate in meetings via teleconference (Zoom PHI) during hemodialysis, and a smaller board facilitated increased participation in a virtual format while members were receiving hemodialysis [30]. Most meetings were done as 1:1 interviews because board members received hemodialysis at different times. Recruitment was conducted at the University of Illinois Hospital and Health Sciences (UI) Health Dialysis Unit using the following inclusion criteria-being >18 years of age, having a diagnosis of ESKD and receiving hemodialysis for >3 months, able to read and speak English, having fatigue (average over the last week) rated ≥4 via visual analogue scale (0 no fatigue, 10 worst fatigue ever experienced), and being able to stand and walk one block. The exclusion criteria were: the individual's nephrologist refused for them to participate, symptoms of unstable cardiac or pulmonary disease in the last month, lower-extremity amputation without prosthetic, orthopedic or neurologic condition that would preclude walking or tensing/releasing of muscles, uncontrolled orthostatic hypotension, and cognitive impairment that precluded participation. All members of the board provided informed consent, and the University's Institutional Review Board approved the study.

The board was queried about their fatigue and feedback about the intervention components, specifically Bernstein and Borkovec's progressive muscle relaxation [31,32] and a walking intervention to reduce fatigue in adults with cancer [33]. Progressive muscle relaxation is a practice where large muscle groups are tensed and relaxed in a specific order while focusing on the feeling of relaxation. The walking intervention sets individualized step goals tailored to the participant's baseline steps per day and gradually increased based on fatigue levels [33]. The content of the interventions, how they were to be combined, proposed intervention delivery methods, and recruitment and retention methods were brought to the board.

Three 1-h meetings took place utilizing a semi-structured script (Appendix A). During the first two meetings, feedback was sought about fatigue and the proposed intervention. At the third meeting, the refined intervention adapted based on their suggestions was presented. After the third meeting, a 1:1 semi-structured interview (Appendix A) was conducted with each member about the refined intervention. The meetings were recorded, transcribed, and imported into NVivo (2020, QSR International) for analysis. Thematic analysis was conducted by two reviewers ([name] & VD), followed by member checking with two participants who represented each theme. Of note, the purpose of the analysis was to inform patient-centered adaptation and enhance intervention feasibility and relevance, rather than to achieve thematic saturation.

### Formative work results

2.1

The patient partnership board (n = 3) was comprised of two females and one male, mean age was 65.3 years (range 30-84), and duration of hemodialysis ranged from 2.5 to 7.5 years.

The board described their fatigue, and three themes (Appendix B) emerged from analysis: (1) fatigue is a multifaceted, mind-body symptom (it was both constant and intermittent (having “good and bad days”), it made you not want to do things, and it had a mental and emotional component), (2) there were few things that made fatigue better (moving around, attitude, and time since the last hemodialysis treatment potentially made fatigue better), and (3) receiving hemodialysis and one's health status made fatigue worse (hemodialysis led to fatigue, as did comorbid health conditions and physical inactivity).

After presenting the two interventions, the board was asked what may hinder or promote engagement with the intervention. Three themes (**Appendix C**) emerged for what may hinder engagement: (1) the participants' attitude, mindset, and mood, (2) the participants’ health status (“good and bad days”, symptoms), and (3) progressive muscle relaxation will require practice. Conversely, when asked about what may promote engagement, six themes (**Appendix C**) emerged: (1) doing both progressive muscle relaxation and increasing steps seemed reasonable, (2) individualized, tailored plan for step goals, (3) individualized plan of when participants would do progressive muscle relaxation, (4) interesting in-person training and make it fun to do, (5) positive feedback and encouragement, and (6) adherence monitoring via technology and self-tracking.

Feedback was also sought about the study fitness watch, accelerometer, website, and text messages. For the fitness watch, the board emphasized the importance of ease of use without an excessive number of buttons and a bright screen. The belt-worn accelerometer was described as the easier device to wear, compared to one applied with a bandage. The board shared the importance of the website reiterating information taught in brief, basic, and straightforward ways with pictures or figures and that audio recordings are helpful. For the text messages, the board thought it would be helpful if messages were encouraging and provided positive feedback, as well as reminders that were easy to read. The board found the attention control topic of reading a nutrition label to be helpful, and information about healthy snacks and why some foods should be avoided were suggested as topics of interest. Regarding survey administration format, in-person administration was most appealing, with phone administered also being reasonable but text-delivered being least ideal.

The board was asked about recruitment and retention. The board unanimously agreed that in-person recruitment was ideal, specifically done during hemodialysis with before or after treatment being alternative options. Positive engagement experiences were said to promote engagement and retention, specifically through interactions between the research team and participants. Encouragement and support from the research team and sharing the benefits of participating were also described as promoting retention. Making the study convenient, with study activities primarily taking place during hemodialysis, and surveys not being overly lengthy, were also described as ways to support retention.

The findings from this formative work informed the development of the *Fight Fatigue* intervention and its associated procedures, which we describe below.

## Study protocol methods

3

### Study design & aims

3.1

The study is a 12-week pilot feasibility randomized controlled trial. The study aim is to investigate the feasibility and acceptability of the *Fight Fatigue* progressive muscle relaxation and walking intervention in adults with ESKD and fatigue receiving maintenance in-center hemodialysis (n = 40). The trial is registered at clinicaltrials.gov (NCT07014111) and approved by the University of Illinois Chicago (UIC) IRB (protocol #2025-0281).

### Study setting & recruitment

3.2

Participants will be recruited from UIC, UI Health, and select dialysis facilities with which the study team has relationships. The study team will review electronic medical records to identify those who meet inclusion criteria identifiable via chart review: age ≥18 years, diagnosis of ESKD and receiving hemodialysis for >3 months, and being able to read and speak English; and have none of the chart-identified exclusion criteria: unstable angina, unstable pulmonary disease or pulmonary symptoms that preclude participation, lower-extremity amputation (below or above the knee amputation) without prosthetic, orthopedic or neurologic condition that would preclude walking or tensing/releasing of muscles, cognitive impairment that precludes trial participation, or any other condition that would preclude participation as deemed by the researchers. We will not include patient partnership board members or patients deemed unable to participate, as determined by their nephrologist. Framed by the recommendations of the board, we will recruit participants by approaching them at the dialysis clinic. If they express interest in learning more about the study, a study staff member will provide them with an informational handout and tell them about the study. Additionally, there will be flyers in the waiting room. A passive mailing or emailing strategy may also be used for recruitment at UI Health.

Interested individuals will be screened in person at the dialysis clinic or over the phone, per the individual's preference, to ensure the individual meets inclusion/exclusion criteria after they provide verbal consent to undergo screening. Screening will consist of clarifying any inclusion or exclusion criteria that were not clear on chart review and asking whether they meet the self-reported inclusion criteria, specifically having a fatigue score ≥4 over the last week measured via visual analogue scale (0 being no fatigue and 10 being extreme fatigue), being able to stand and walk one block, and having a cell phone that can receive text messages. Individuals meeting eligibility will be offered the opportunity to complete the consent process and be enrolled.

### Randomization

3.3

Participants will be randomized after consent and baseline testing are completed. The REDCap randomization module will be designed by the study statistician. Randomization will be stratified based on baseline fatigue scores as measured by the Functional Assessment of Chronic Illness Therapy-Fatigue (FACIT-F) scale (FACIT-F score <30 vs. **≥**30). Randomization within each stratum will be 1:1 to each of the two groups, utilizing a block randomization scheme (block size 4). The study statistician will create this allocation schedule.

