### Blinding

3.4

Due to the nature of behavioral research, blinding will be done to the extent possible, given the nature of this work. The statistician will be blinded to the meaning of the randomization allocation labels (“1” and “2”). The outcomes assessor will be blinded to the extent possible when assessing patient-reported outcomes at weeks 6 and 12 (e.g., fatigue). The research team members delivering the intervention will not be blinded due to the nature of the intervention.

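### A single published block size of 4 within each FACIT-F stratum lets a team member who tracks earlier allocations deduce up to one third of assignments once the baseline FACIT-F is scored

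*Protocol article*

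**What the plan says.** All references are to the protocol article.

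- **Scheme (section 3.3, Randomization).** "Randomization will be stratified based on baseline fatigue scores", with a cut at 30 on the FACIT-F, which gives two strata. "Randomization within each stratum will be 1:1 to each of the two groups", "utilizing a block randomization scheme (block size 4"). No other block size is mentioned.
- **Timing and system (section 3.3).** "Participants will be randomized after consent and baseline testing are completed". "The REDCap randomization module will be designed by the study statistician", and the statistician also prepares the schedule.
- **Blinding (section 3.4).** "The research team members delivering the intervention will not be blinded due to the nature of the intervention". The statistician does not know what the group labels mean. The outcome assessor's blinding is stated for weeks 6 and 12 and only as far as possible. Nothing is said about blinding whoever collects the baseline FACIT-F.
- **Recruitment (section 3.2).** "we will recruit participants by approaching them at the dialysis clinic". The person who does this is described only as a member of study staff. The article does not say whether that person also delivers the intervention or sees earlier allocations.

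**The concern.** A computerised module hides the allocation list. It cannot hide an allocation that follows from the ones already made. With one known block size of 4, the last assignment in every block is forced by the first three, and the third is forced whenever the first two match. Unblinded delivery staff see assignments as they accrue. The arm may also be visible to others at the clinic, because intervention participants use a study watch during the trial while controls receive theirs at the end (sections 3.5 and 3.7).

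The stratum is fixed by the baseline FACIT-F, so the relevant window runs from baseline scoring to randomisation. Baseline also includes one week of ActiGraph wear (section 3.8.2), and the order of the baseline measures is not stated. If the FACIT-F comes first, the window could last a week or more. Within it, foreknowledge could influence the order in which waiting patients are randomised, whether a patient withdraws late, or how a FACIT-F score near 30 is handled.

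Two planned outputs depend on who enters the intervention arm: adherence to relaxation sessions and step goals (target above 70% among retained participants) and the within-group variability of FACIT-F change, which is to be used to power the next trial (section 3.9).

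**Working it through.** The article gives no predictability figure, so there is none to reproduce.

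**Inputs.** Block size 4, ratio 1:1, two strata (section 3.3); 40 participants (section 3.9.1). Assumption: the observer knows the block size and every earlier allocation in the stratum.

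**1. Stratum known, fixed blocks of 4.** A block holds two of each arm, so there are C(4,2) = 6 equally likely orderings. The probability that a position is forced is:

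| Position | 1 | 2 | 3 | 4 |
|---|---|---|---|---|
| Forced | 0 | 0 | 1/3 | 1 |

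The share certain in advance is (0 + 0 + 1/3 + 1)/4 = 1/3, and 40 × 1/3 = 13.3 allocations. A simulation of 40 patients in two strata, allowing for incomplete last blocks, gives 31.2%, or 12.5 of 40.

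**2. Best guess, fixed blocks of 4.** The probability of a correct guess is 1/2 at position 1, 2/3 at position 2, 1/3 × 1 + 2/3 × 1/2 = 2/3 at position 3, and 1 at position 4. The mean is (1/2 + 2/3 + 2/3 + 1)/4 = 17/24 = 70.8%.

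**3. Stratum not yet known (approach or consent).** The next arm is then certain only if both strata are at a forced position and force the same arm. Treating the strata as independent, this is roughly 1/3 × 1/3 × 1/2 = 1/18 = 5.6%. The simulation of 40 patients gives 5.2% with an even split between strata (40 × 0.052 = 2.1 allocations), 5.0% with a 30:70 split and 3.8% with a 10:90 split. The figure would be somewhat higher if the screening fatigue rating helps staff guess the stratum.

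**4. Alternatives, stratum known.** For mixed sizes the observer is assumed to know the set of sizes but not their order, with 20 patients per stratum (simulated). Fixed sizes are exact.

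| Scheme | Certain | Of 40 | Best guess correct |
|---|---|---|---|
| Fixed 4 | 33.3% | 13.3 | 70.8% |
| Fixed 6 | 25.0% | 10.0 | 68.3% |
| Fixed 8 | 20.0% | 8.0 | 66.6% |
| Random 4/6 | 5.7% | 2.3 | 68.5% |
| Random 4/6/8 | 2.5% | 1.0 | 67.2% |

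An observer who does not know the set of sizes can be certain no more often than this.

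**5. What one steered patient could do.** With about 20 allocated to the intervention and 80% retained (section 3.9.1 anticipates attrition of at most 20%), the adherence denominator is about 16. If adherence is counted per participant, which is an assumption, exchanging one non-adherer for one adherer moves it by 1/16 = 6.25 percentage points.

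**6. Cost in balance.** An incomplete last block of 4 leaves an imbalance of at most 2 in a stratum. With a block of 6 the maximum is 3.

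**The case against.** A reader might infer that recruiters know a third of allocations while choosing whom to approach at the chair. The article does not support that, for two reasons.

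- Only those who deliver the intervention are said to be unblinded. Overlap with recruiting staff is plausible in a small team, but it is not stated, and separation of roles may be described in the full protocol.
- The stratum is unknown at approach. Screening uses a 0 to 10 rating, not the FACIT-F, and randomisation waits for completed baseline testing, so other patients may take the next slot first. The figure for that stage is about 5%.

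A reader might also infer broad damage to the trial's results. That goes too far as well. The recruitment ratio is settled before randomisation, the retention target covers all randomised participants and is not an arm comparison, and the Discussion disclaims any test of efficacy.

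Two further objections stand. Varying the block size barely reduces guessability: 70.8% to 68.5% is about one allocation in 40, and someone inclined to steer can act on a likely guess. And small fixed blocks are a defensible way to keep balance with 40 patients in two strata of unknown size; nothing in the section is contradictory or miscalculated.

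These objections limit the point but do not remove it. Computerised release after baseline does not prevent deduction from past allocations, and the intervention-arm adherence figure and the within-group FACIT-F change remain exposed.

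**Conclusion.** The point holds as a possible exposure with an inexpensive remedy. Up to one third of assignments, about 13 of 40, can be deduced with certainty between baseline FACIT-F scoring and randomisation. Before the stratum is known, the share is about 5%. One third is an upper bound: it needs someone who knows the block size, every earlier allocation in that stratum across all facilities, and the patient's stratum. Whether anyone who enrols patients is in that position cannot be settled from the article. The outputs at risk are adherence in the intervention arm and the within-group FACIT-F change. The size of any resulting bias cannot be estimated from the document; the 6-point shift per exchanged patient shows only how sensitive a denominator of about 16 is.

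**What to change.** Have the statistician generate the REDCap allocation table with block sizes varied at random, for example 4 and 6, within each FACIT-F stratum. In section 3.3, replace the stated size with a sentence that block sizes vary and are withheld from enrolling and delivery staff. If recruitment has already begun, the change can apply from the next unopened block in each stratum.

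The cost is a new table, one sentence, and a possible end imbalance of 3 instead of 2 per stratum. The gain is mainly the removal of certainty (33% to about 6%), with little change in best-guess accuracy. Keeping enrolment and baseline scoring with staff who do not see earlier allocations would address the guessing as well. If that separation already exists in the full protocol, saying so in section 3.4 would largely answer the point.

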### Blinding

3.4

Due to the nature of behavioral research, blinding will be done to the extent possible, given the nature of this work. The statistician will be blinded to the meaning of the randomization allocation labels (“1” and “2”). The outcomes assessor will be blinded to the extent possible when assessing patient-reported outcomes at weeks 6 and 12 (e.g., fatigue). The research team members delivering the intervention will not be blinded due to the nature of the intervention.

### Interventions

3.5

***Fight Fatigue*-** The *Fight Fatigue* intervention was informed by two evidence-based interventions (progressive muscle relaxation [31,32] and an increased step count intervention [33]), through our work with a patient partnership board, and guided by the Information-Motivation-Behavioral Skills Model [34]. We combined and refined these interventions to meet the needs and preferences of adults with ESKD, as described above. Refinements suggested by the board were integrated if they aligned with the goal of the intervention (reduce fatigue), maintained the fidelity of the evidence-based interventions, aligned with the guiding theory (Information-Motivation-Behavioral Skills Model), and did not increase participant risk. The intervention delivery is framed by the Information-Motivation-Behavioral Skills Model to support behavior change by providing information to support knowledge, identifying and addressing factors that influence motivation, and assuring that participants have the necessary skills to perform the intervention activities [34].

The *Fight Fatigue* intervention is delivered via two, scripted in-person education/training sessions followed by text messages. During the in-person sessions, participants will learn and practice progressive muscle relaxation and how to increase steps, as well as be provided with written instructions and a place for tracking progressive muscle relaxation times and reaching one's step goal. Progressive muscle relaxation training will begin with a description of the rationale for progressive muscle relaxation, followed by training and demonstration of the tension/relaxation 16-muscle sequence [31,32]. After learning the 16-muscle sequence, the 7- and 4-muscle sequences will be taught [31,32]. Participants will be instructed not to tense/relax muscle groups that are injured or cause pain. After the first training session, participants will be instructed to practice progressive muscle relaxation for 20 min at least 2 days/week. Each participant will receive a unique login to a study-specific website that contains recordings of the progressive muscle relaxation 16-, 7-, and 4-muscle sequences. Progressive muscle relaxation recordings have been used in other studies integrating home-based progressive muscle relaxation [35].

The increasing steps training will consist of learning about taking steps (walking) at light intensity (Borg rating of perceived exertion 2-3). Participants will be given and taught how to use a fitness watch (i.e., Garmin vivosmart). Fitness watches have been used in other interventions aimed at enhancing physical activity among those with ESKD [36]. The fitness watch will be set up by study staff and associated with a deidentified account. Study staff will sync the device throughout the study (approximately every 1-2 weeks). Participants will be given an individualized step goal based on their baseline step count and tailored to their level of fatigue, as has been done in other work [33]. The baseline steps will be determined by one week of wear of the fitness watch (worn with screen not visible to participants). To be included in the calculation of baseline steps, a valid day will be considered to have at least 10 h of wear time, as used in other studies that have utilized consumer wearable technologies in those receiving hemodialysis [37]. Each week, participants will be asked what their fatigue level has been over the last week (rated via visual analogue scale; 0 no fatigue, 10 extreme fatigue). Of note, this weekly fatigue measurement is used for intervention tailoring and is not a primary outcome measure. If a person's fatigue level remains unchanged or improved (from one week to the next), the step goal will be increased, as done by the intervention [33] guiding this component of *Fight Fatigue*. Specifically, if a participant's baseline steps are >7000 steps, the increase would be 0%; if baseline steps are 5001-7000 steps, the increase would be 2.5%; if baseline steps are 2500-5000 steps, the increase would be 5%; and if baseline steps are <2500, the increase would be 7.5%. If fatigue worsens from one week to the next, the step goal for the following week is not increased [33]. Participants will be encouraged to reach their step goal at least two days per week. Participants will be instructed to contact study staff if they have any questions about increasing steps, the fitness watch, and they will be instructed to stop walking if they experience any chest pain, shortness of breath, or otherwise feel unwell.

***Attention Control-*** We will be controlling for contact, not content, in our attention control condition of ESKD Education (information on how to read a food nutrition label). This topic was chosen because it does not influence fatigue and was endorsed by the board as a topic of importance and interest. The attention control condition will be delivered via two, scripted in-person sessions, followed by text messages.

